### Covariates

Covariates are the moderating factors identified in the study conceptual framework. Covariates that show significant association with the variables of interest under consideration will be controlled for using multiple logistic regression. These include maternal characteristics such as; age, parity, pregnancy status, cesarean section, educational status, twin pregnancy, income level, abortion, and marital status. These will be adjusted for as confounding using logistics regression models. Population characteristics such as wealth index, distance, region, educational status, and rural/urban residence will also be adjusted for as confounding variables [42].

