### Demographic and health survey data

Demographic and Health Survey data sets are a household survey collected using a two-stage sampling method. Clusters for the sampling in Ghana used sampling frames of the 2000 and 2010 population and housing census to sample for the 2008 and 2014 DHS surveys respectively. For 2008, 412 clusters were determined in the first stage. In the second stage, 29 households were selected from each of the 412 clusters. Household from one cluster data was left out due to ethnic conflict at the time, thus 12, 323 households were selected.

The 2014 DHS also determined 427 clusters; 216 urban areas and 211 rural areas. The second stage then sampled 30 households per cluster for questionnaire administration in each household, thus, 12,831 households, similar to the sampling technique for the 2008 DHS.

In both situations, women between the ages of 15 and 49, who were either permanent residents in the selected households or stayed in the household the night before the selection were eligible to participate in the study and had their blood pressure measured. Sampling excluded women living in barracks, hotels, and prisons. Children between 0 and 59 months were also eligible and had their height and weight checked.

Eligible women participated in the study and answered questions on; age, pregnancy status, education, and relationship to the household head, residence, birth history, parity, pregnancy outcomes, knowledge and use of family planning methods, malaria interventions, diarrheal diseases, antenatal care and facility, and facility delivery (children born within the last 5 years).

Whereas GDHS 2008 collected data on the NHIS, the GDHS 2014 collected information on the free maternal health policy. Ghana and Kenya DHS surveys are similar in sampling procedures and methods and therefore comparable. DHS surveys are considered alternative to population and housing census in many situations due to their wide range of coverage in public health and socio-economic variables.

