### Variables of interest

The maternal healthcare utilization examines two primary outcome variables which include; antenatal care up-take (4+ visit = 1, and ≤ 3 visits = 0), and facility delivery utilization, also binary outcome (facility delivery = 1 and home delivery = 0). Mothers’ health insurance status (proxy to the FMHCP) is the exposure variable of interest in this study.

Stillbirth, perinatal death, and neonatal mortality are secondary outcome variables of interest generated as binary outcomes from the DHS data sets using variable *b6,* and *b7* against which the policy utilization impact will be measured. Table 5 presents the derived variables generated using STATA 15.0 from the 2008/2014 DHS data sets.

**Table 5 Tab5:** Variables of interest

Item	Label	Name	Recoding	Binary V
1	Respondent holds valid NHIS card	*S1015*	Holds a valid NHIS card (with or with no evidence) = 1 No valid NHIS card = 0	*Vid_1*
2	Respondent hold valid NHIS card	*S1015*	Holds a valid NHIS card (with evidence) = 1 No valid NHIS card plus (holds a valid NHIS card with no evidence) = 0	*Vid_2*
3	Number of ANC visit during pregnancy	*m14*	Antenatal visits 0–3 = 0 Antenatal visits ≥ 4 = 1	*anc4*
4		*m15*	Home delivery = 0 All facility delivery = 1	*fdelivery*
5	Age at death	*b6*	Alive after day 0 = 0 Born dead/died on day 0 = 1	*stillbirth*
6	Age at death	*b6*	Did not die before 7th day = 0 Died before 7th day of life = 1	*prdeaths*
7	Age at death (months imputed)	*b7*	Did not die before 28th day = 0 Died before 28th day of life = 1	*neodeaths*

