### Exposure variables

The National Health Insurance status [proxy to the ‘free’ maternal healthcare policy (FMHCP)] is the main exposure variable. However, on the secondary level of analysis, antenatal care up-take (binary) and facility delivery utilization (also binary) are independent predictors, through which the secondary outcomes of interest; stillbirth, perinatal death, and neonatal death can be measured.

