### Data analysis

The secondary data will be cleaned and organized, dropping irrelevant variables and renaming covariates for ease of reference as necessary. Essentially, variables of interest in this study are binary outcomes i.e. 1 = case/the presents of an intervention, and 0 = no case, the absence of intervention, control.

Both multivariate logistic regression and Poisson with robust standard error, or negative binomial regression depending on whether there is over dispersion (conditional variance exceeding the conditional mean) will be fitted and analyzed. Thus, **loge** {*p*1 / *(1—pi)*} = *b0* + *b1 Xi1* + *b2 Xi2* + … + *bkXik*. The Use of the multiple logistic regression model also comes with the advantage of adjusting for confounding by including the covariates in the model.

For the matching method, Ghana’s DHS data sets (2008 and 2014) will be merged. This will increase the sample size to n = 8876, and add power to the study. The merger will also eliminate the risk of lack of common support, the so-called curse of dimensionality, a common phenomenon in propensity score matching, where treated units propensity scores cannot find suitable pairs.

Descriptive data will be presented using tables, frequencies, and proportions. The data will then be analyzed distinctly, using multiple statistical models and quasi-experimental design techniques. Firstly, the student independent *t*-test will be used to test for proportions, the significance of association, and mean differences between the independent variable, and the binary outcomes of interest; antenatal care uptake, and facility delivery utilization.

Test of association set < 0.05 less of significance, between the secondary variables of interest (stillbirth, perinatal death, and neonatal mortality) and the covariates; mothers age, marital status, level of education, wealth index, region, area of residence, twin delivery, parity, and employment status will be determined by using the Rao Scot Chis-square, which has an added sensitivity advantage, while adjusting for complex survey design features (weighting, clustering and stratification).

Only covariates found to be significantly associated with the dependent or independent variables will then be included in a multiple logistic regression model and adjusted for confounding [72].

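### Caesarean section and pregnancy status are listed as confounders although they follow the exposure or the outcome, and the two covariate lists in the protocol conflict on them

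*Protocol article*

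**What the plan says.** The Covariates section lists the maternal characteristics "age, parity, pregnancy status, cesarean section, educational status, twin pregnancy, income level, abortion, and marital status" and continues: "These will be adjusted for as confounding using logistics regression models". Entry depends on a significant association with the variables under study.

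The Data analysis section names the covariates to be tested against stillbirth, perinatal death and neonatal mortality: "mothers age, marital status, level of education, wealth index, region, area of residence, twin delivery, parity, and employment status". It then states: "Only covariates found to be significantly associated with the dependent or independent variables will then be included in a multiple logistic regression model". Neither section limits covariates to those that precede the exposure.

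Facility delivery has two roles. It is a primary outcome, coded "facility delivery = 1 and home delivery = 0" (Variables of interest). At the secondary level, "antenatal care up-take (binary) and facility delivery utilization (also binary) are independent predictors" of the three death outcomes (Exposure variables).

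On timing, the section on the Demographic and Health Survey data says: "Eligible women participated in the study and answered questions on; age, pregnancy status, education". The delivery questions in the same interview cover births of the preceding five years.

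**The concern.** A confounder must come before the exposure. A caesarean cannot precede the choice of place of delivery: it is done only in a facility, and often because of a complication that also raises the risk of death. Every home birth therefore has caesarean = 0. Once caesarean is in the model, the facility coefficient sets all home births against facility births from which many complicated deliveries have been removed. Pregnancy status at interview comes later still, after the birth and after any death, and may itself depend on whether the baby survived.

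At stake are objective 3 and the second and third hypotheses (facility delivery and death), and the adjusted model for the primary outcome facility delivery. The Expected outcome section anticipates a favourable policy effect, so a spurious protective estimate could be read as confirmation.

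**Working it through.** **1. The plan's own figure.** Merged Ghana sample: 2992 + 5884 = 8876, as stated. It serves below only as the n of an illustration. The protocol gives no figure on the covariate question, so every other input is an assumption unless a source is named.

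**2. The two lists.** Caesarean section and pregnancy status are both in the Covariates section and both absent from the Data analysis list for the death outcomes. That section gives no separate covariate list for the two utilization outcomes, so for facility delivery as outcome only the Covariates list speaks.

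**3. Caesarean in a death model, no true facility effect.** Let c be the share of complicated births (equal at home and in facilities), d1 and d0 the death risk with and without complication, and a and b the caesarean share among complicated and other facility births. The complicated share among non-caesarean facility births is

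w = c(1−a) / [c(1−a) + (1−c)(1−b)],

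and the comparison with home births is

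RR = [w·d1 + (1−w)·d0] / [c·d1 + (1−c)·d0].

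| c | d1 | d0 | a | b | RR (truth 1.00) |
|---|---|---|---|---|---|
| .10 | .10 | .015 | .40 | .05 | 0.0206/0.0235 = 0.88 |
| .15 | .10 | .01 | .50 | .05 | 0.0176/0.0235 = 0.75 |
| .10 | .15 | .01 | .60 | .03 | 0.0161/0.0240 = 0.67 |
| .15 | .15 | .01 | .60 | .03 | 0.0195/0.0310 = 0.63 |

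These rows use strong links between complication, caesarean and death. A second set fixes deaths at 30 per 1000 (the 2008 Ghana neonatal rate in the section on Kenya as comparison country) and uses weaker links.

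- Middle case: 65% facility births, 10% complicated, caesarean in 15% of facility births, complication multiplying caesarean by 4 and death by 5. Caesarean risk is .15/(.9 + .4) = .115 without and .462 with complication. Death risk is .03/(.9 + .5) = .0214 without and .107 with. Non-caesarean facility births then have a death risk of .0269 against .0300 at home, so OR = 0.89.
- Stronger case (20% complicated, caesarean 20%, multipliers 4 and 8): .0234 against .0300, OR = 0.78.
- Grid (facility 60–75%, complicated 5–20%, caesarean 10–20%, multipliers 2–6 and 3–8): OR 0.68 to 0.99.
- If complication drives only caesarean or only death, OR = 1.00.

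At n = 8876 and a two-sided 0.05 level (sidedness assumed), the chance of a significant protective result under the null is 13% in the middle case and 43% in the stronger one, against 2.5%. With an assumed design effect of 1.5 these become 10% and 31%. Over the grid, without a design effect, the chance is 3% to 74%.

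Adjustment can also hide a real benefit. If caesarean halves deaths and is unrelated to risk, the facility OR of 0.92 becomes 1.00 after adjustment.

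**4. Unequal complication rates.** In the middle case, but with 15% complicated births in facilities and 10% at home, the null OR is 1.15 unadjusted and 1.01 adjusted for caesarean.

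**5. Facility delivery as outcome.** The cell caesarean = 1, home delivery is empty by definition, while caesarean = 0 holds both home and facility births. That is quasi-complete separation: the logistic caesarean coefficient has no finite estimate.

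**6. Propensity model for facility delivery.** The probability of facility delivery given caesarean is 1, so no home birth can match. The Data analysis section expects merging the two surveys to remove common-support problems, but pooling cannot fill a cell that is empty by definition.

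**7. Pregnancy at interview, no true facility effect.** Assumed: 6–15% pregnant, death raising later pregnancy 1.5- to 4-fold, the same in facility and home births.

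| Effect of facility delivery on later pregnancy | Adjusted OR for death |
|---|---|
| Lowers it (ratio 0.6–0.8) | 1.01 to 1.23 |
| None | 1.00 |
| Raises it (ratio 1.2) | 0.89 to 0.99 |

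If the effect of a death on later pregnancy may differ between facility and home births, the range is 0.88 to 1.28.

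**The case against.** **The death models may never contain these variables.** The Data analysis list for the deaths omits both, and the screening rule follows directly after that list. A reader might infer from the Covariates section that caesarean section will always be selected into the death models. The documents do not support that: on the Data analysis text it is not a candidate. What stands is a conflict between two sections, one of which prescribes a harmful adjustment. If the Covariates list governs, the screen gives little protection, because caesarean is tied to facility delivery by definition.

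**The direction is not fixed.** A reader might infer that the bias is always protective. That holds for caesarean only when complication rates at home and in facilities are similar. In step 4, leaving caesarean out gives an estimate further from the truth. This objection stands against any claim about direction. It does not make caesarean a confounder: the near-cancellation depends on the inputs and would itself be an accident.

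**Pregnancy status.** Its timing at interview is inferred from the survey description and is not stated in the Covariates section. Nothing supports a protective direction for it.

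**Separation is limited.** It is quasi-complete, not complete. The Poisson model with robust standard errors, also planned, does not suffer separation from a stratum in which every birth is in a facility.

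**The sizes rest on assumptions.** That is so, and weak links between complication, caesarean and death give values close to 1.

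**Conclusion.** The point holds as a conflict between the Covariates and Data analysis sections, in which the Covariates version treats two variables as confounders that cannot be confounders of facility delivery and death. For caesarean section, adjustment under the null gives an OR or RR of about 0.63 to 0.99, given equal complication rates at home and in facilities and the assumed inputs shown. With more complicated births in facilities, the biases can partly offset. Quasi-complete separation in the logistic model for facility delivery, and the absence of home matches if facility delivery is the matched treatment, need no assumed inputs beyond caesareans being done only in facilities. For pregnancy status, provided it means status at interview, bias can go either way and is nil if facility delivery does not affect later pregnancy.

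A reader might extend this to parity or abortion. The working here does not show harm from those variables.

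**What to change.** - Delete caesarean section and pregnancy status at interview from every adjustment and propensity model.
- State one prespecified list of covariates that precede the exposure, and use it in both the Covariates and the Data analysis sections.
- Report caesarean section descriptively only.

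The cost is protocol wording, with no new data and no loss of sample.

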### Scope and limitations

This study is limited in scope, as it will not estimate the free policy impact on maternal mortality. Even though the gold standard for policy impact evaluation is randomization, the FMHCP policy implementation was without randomization due to its characteristic; a social policy targeting everyone, particularly, the vulnerable and less privileged, thus, the strength of randomization as contained in a prospective design is a limitation in this design.

Again, Yin averred that the essence of a qualitative study is to generate a deeper understanding of a phenomenon rather than to generalize and that, any generalization should be done with caution and only in settings of similar characteristics [71]. Yin observation is applicable in the context of the qualitative design.

### Ethical considerations

This protocol received approval from the Ghana Health Service Ethics Review Committee (Reg. No. GHS-ERC: 002/04/19). Data access has also been granted by MEASURE DHS, after completing registration. Access to Ghana and Kenya Demographic and Health Survey data sets for the study period is approved (letter attached).

Data handling comply with the GHS-ERC protocol requirement and the ethical standards of MEASURE DHS, with no third party use. Data will be used only for the project and under the approved project title and regulations of the University of Ghana Public Health School. DHS data sets are anonymous, thus, there will be no attempts to identify communities, households, or individuals who participated in the respective surveys.

Terms of data use are referenced at https://dhsprogram.com/Data/terms-of-use.cfm. Where necessary, an electronic PDF copy of any publications from this study will be sent to [contact]. All study participants will sign a consent form before participating in the interviews and group discussions.

Pregnant women participants will have their vital signs checked and recorded by a registered nurse, to ensure their health status meets a set of healthy criteria before they can participate in the FGD (Table 4). Participants’ identity will be protected and voice recording immediately transcribed into hard copies and the content discarded. All study participants will receive a Participants Information Sheet certified by the GHS-ERC.

Study participants will also have the right to withdraw from the study before or during the data collection process with no prior notice. The GHS-ERC approval letter together with an official permit from the University of Ghana Public Health School will be used to gain entrée to all primary data collection points for the qualitative data gathering.

### Protocol implementation

This protocol will be implemented in phases as per the design. Proposal writing preceded the protocol’s approval and the approved protocol will be implemented as outlined in Table 6 (see Additional file 1). The implementation will also be monitored by the Ghana Health Service Ethics Committee, as well as the supervisory committee of the University of Ghana Public Health School. The approved protocol follows the standard of research required for the award of a doctoral degree set out by the University of Ghana.

**Table 6 Tab6:** Protocol implementation, monitoring & evaluation

Phase I	Phase II	Phase III
*Review of relevant literature on;* Maternal health care policy Maternal health care utilization Burden of stillbirths Perinatal deaths Neonatal mortality *Retrieval of secondary data from MEASURE DHS;* Ghana DHS 2008 Ghana DHS 2014 Kenya DHS 2008 and Kenya DHS 2014 *Cleaning and organization of DHS data:* Dropping of irrelevant variables Merger of data sets *Variable management* recoding and renaming *Preliminary analysis of DHS data (secondary data)* Hypothesis testing Analysis of association and Determination of significant levels (set at ≤ 0.5)	Gaining entrée for primary data collection *Primary data collection* In-depth interviews (IDIs) of service providers Focus Group Discussion (FGD) among pregnant women *Preliminary analysis of qualitative data* Data transcription Annotation of significant statement Coding and Categorization of common themes *Key Informant Interviews* Transcription of key informant interviews *Triangulation of data* Drawing congruence of policy user Perspective/perception, Service provider perspective and Policy implementers view points	*Presentation of preliminary findings and feedback at;* Institutional level Clinical forum ANC clinic to policy users *Summary presentation at;* Regional Annual Performance Review *Presentation of final report at;* School of Public Health, University of Ghana *Publication of Final report for policy actors, research and scientific community in;* MOH reports NHIA report Internal journals Local journals Policy briefs
Monitoring and evaluation of phase I, II, and III		
Guidance and comments of Co-investigator 1,2 and 3	Guidance and comments of Co-investigators 1 and 2	Scheduling of presentation Purview of Co-investigators and faculty of Health Policy Planning Management of the University of Ghana Public Health School

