### Data source and size

Ghana and Kenya 2008/2014 DHS data sets are collected about the same time by MEASURE DHS, a USAID sponsored program. DHS used a similar questionnaire of international standards to collect the 2008/2014 data sets, which serves as the main data source for this study. The advantage of using DHS data has been widely documented [62, 63]. DHS collects wide and multipurpose data with a standard questionnaire which includes health indices and contains variables relevant for this current study.

Children data sets, KR data, collected data from women in household settings within their reproductive ages of 15–49 years of both countries will be used for the quantitative analysis. Cross country data analysis will only be required at the stage of the quantitative analysis owing to the DID method.

However, primary data will be collected from one selected region in Ghana, the Upper East Region, based on the odds of coverage of the ‘free’ policy, for an in-depth description of the policy in the real-world setting. This is relevant to add context to the study findings and empower the discussion. Ghana’s data sets are represented by the 2008/2014 GDHS data collected from 12,323/12,831 households respectively using a two-stage sampling technique.

Kenya, on the other hand, is represented by the KDHS data sets of 2008/2014, also collected using two-stage sampling design from a representative household sample of 9936/40,300 from 400 clusters (133 urban, 267 rural) and 1612 clusters (997 rural, and 617 urban) for the 2008/2014 respectively [45, 48].

In total, the sample size of Ghana 2008/2014 DHS data are n = 2992/5884, whereas, those of Kenya are n = 6079/20,964 for the 2008/2014 respectively. The two countries' data sets were collected, approximately 6 years into the implementation of the ‘free’ maternal healthcare policy in Ghana, and considered adequate and representative in size to power the study.

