Logistics regression is considered appropriate, giving the binary status variables of interest; antenatal care up-take [yes = 1 (ANC visit ≥ 4)] and [no = 0 (ANC visit of ≤ 3]; facility delivery utilization [yes = 1 (facility delivery) and no = 0 (home delivery)], and the secondary outcome variables; stillbirth, perinatal and neonatal deaths, generated through the re-coding of the relevant variable *m14, m15, b6, b7*, and *s1015,* from the DHS data sets (Table 5).

The treatment difference will be determined through nearest-neighbor matching of treated and untreated units’ propensity scores generated ex-post, and using logistics regression while controlling for the confounding variables for precision. The 'free' policy impact will then be determined using the average treatment effect on the treated. Robustness of results will be achieved with reduced standard errors using bootstrapping replication while testing for sensitivity using a t-test of bias, and probit regression.

Of the treatment and comparison country analysis, the DID analysis will be used to determine the policy impact, using the 2008 data set of the two countries (Ghana and Kenya) as a baseline and 2014 data sets as the end line. The study is powered by the sample size calculation, originally determined by the survey design. The sample size is n = 2992/5884 (8,876) for Ghana DHS 2008/2014 data sets, and n = 6079/20,964 (27,043) for Kenya DHS 2008/2014 data sets respectively.

Clustering and stratification will be adjusted for using sample survey weighting at all stages of the analysis. This will produce unbiased treatment estimate that can be generalized to the original survey population [26, 52].

The qualitative data will be deductively analyzed using predefined themes. However, common themes that emerges from the interviews and focused discussion will be organized as sub-themes and inductively reported. The approach will be aided by NVIVO 12, through which nodes and their children will be created to categories significant statements into similarities and dissimilarities [73].

The results of the primary data will be reported using the common themes approach with word frequency count and cloud, and vivid quotations to back themes. The inclusion of qualitative data will add context and situate the discussion with explanatory power to the statistical findings [48].

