## Discussions

The study design and methodology will be discussed as deliverables outlining the methodological strength and limitations for future researchers. Multistage discussions will be employed adequately and distinctly, in reporting the study findings. The predictive abilities of the variable and the covariates in the multiple logistic regression model will be thoroughly examined along the lines of statistical significance levels, set at p < 0.05. The study discussion will also compare and contrast the current result with exiting literature for congruence or divergence.

The effects of facility delivery utilization i.e. antennal clinic attendance and health facility delivery will be discussed in the context of financial accessibility and universal health coverage. Stillbirth and perinatal deaths outcomes will be modeled to make predictions and projections in the discussion stage and inferred on targets such as achieving sustainable development goal 3.

The discussion will also look at the ‘free’ policy effectiveness and impact, drawing lessons from the qualitative result in the context of lower/middle income country, and the overall objectives of social health insurance in developing country context to inform policy development in other countries, particularly, Sub-Saharan Africa.

In the qualitative stage, discussions will follow the thematic inductive approach, where meanings from participants’ views are compared to existing literature to establish similarities and dissimilarities. The discussions are expected to identify policy implications from the results to inform practice and research. Discussions will isolate key study findings and highlight the contribution of the study to knowledge and policy, i.e. what is known from the study, in an attempt to address the research objectives and gaps.

Conclusions will be drawn for policymakers and recommendations made for policy, practice, and research. Within the study context, the conclusions will take the shape of the data as it is compared to existing literature, mirroring Lipsky's theory of Street-Level Bureaucracy to draw lessons for future design and implementation of a similar intervention in similar settings.

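### Table 6 sets significance at 0.5 where the text says 0.05; separately, the general claim of adequate power is not supported for the mortality outcomes

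*Protocol article*

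**What the plan says.** **Significance level.**
- Protocol implementation, Table 6, Phase I, listed with hypothesis testing and analysis of association: "Determination of significant levels (set at ≤ 0.5". The paragraph introducing the table says the approved protocol will be carried out as the table sets out.
- Data analysis: "Test of association set < 0.05 less of significance, between the secondary variables of interest" and the covariates. The same section adds: "Only covariates found to be significantly associated with the dependent or independent variables will then be included in a multiple logistic regression model".
- Discussions, on the multiple logistic regression model: "along the lines of statistical significance levels, set at p < 0.05".

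**Power.**
- Data source and size: the data sets are "considered adequate and representative in size to power the study".
- Data analysis: "The study is powered by the sample size calculation, originally determined by the survey design".
- No effect size, target power or design effect is given for any outcome.

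Antenatal care uptake and facility delivery are the primary outcomes. Stillbirth, perinatal death and neonatal mortality are secondary.

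**The concern.** **Significance level.** The current text carries two decision thresholds that differ by a factor of ten, and the looser one stands in the table that schedules the hypothesis tests. The two statements of 0.05 are each tied to a particular use: outcome–covariate association tests in one place, the logistic regression in the other. For the t-tests on the primary outcomes, the DID and the matched treatment effect, the text states no level, so Table 6 is the nearest rule. A reader who applied it literally would declare half of all true null hypotheses significant.

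**Power.** The article makes a positive claim of adequate power; it does not merely leave out a calculation. A household survey's sample size calculation does not in itself establish power for a four-cell, two-country contrast on deaths occurring at about 3%. The overall study goal includes impact on perinatal outcomes, and two of the three null hypotheses concern perinatal deaths. A reader relying on the general claim would expect more from the mortality comparisons than the sample can give.

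**Working it through.** **1. Threshold**

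| Place | Level | Tests it is worded for |
|---|---|---|
| Table 6, Phase I | ≤ 0.5 | hypothesis testing, analysis of association |
| Data analysis | < 0.05 | mortality outcomes against covariates |
| Discussions | < 0.05 | multiple logistic regression model |
| Data analysis: t-tests on primary outcomes, DID, matching | none stated | – |

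0.5 / 0.05 = 10.

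**2. Power**

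The plan states no power figure, so there is none to reproduce. Its sample totals do check: 2992 + 5884 = 8876 and 6079 + 20,964 = 27,043.

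Inputs from the document:
- n = 2992 / 5884 (Ghana 2008/2014) and 6079 / 20,964 (Kenya 2008/2014), from Data source and size;
- neonatal mortality of 30 (Ghana) and 31 (Kenya) per 1000, from Kenya as a comparison country;
- the DID estimator, from Statistical methods and rationale, Table 2.

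Assumptions, none of them in the document: two-sided 0.05, 80% power (1.960 + 0.842 = 2.802), design effect (DEFF) from 1 to 2, and the stated n used as denominators.

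*DID, neonatal death.* Detectable change = 2.802 × √(DEFF × Σ p(1−p)/n).
- Ghana: 0.030 × 0.970 × (1/2992 + 1/5884) = 0.0291 × 0.00050418 = 0.00001467
- Kenya: 0.031 × 0.969 × (1/6079 + 1/20,964) = 0.030039 × 0.00021220 = 0.00000637
- SE = √0.00002105 = 0.00459
- Detectable change = 2.802 × 0.00459 = 0.01285, about 12.8 per 1000. Relative to 30 per 1000 this is 42.8%.

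If the Ghana 2014 variance is taken at the reduced rate instead, the change is 12.2 per 1000 (40.8%).

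| DEFF | Reduced-rate variance | Equal variance |
|---|---|---|
| 1 | 12.2 per 1000 (41%) | 12.8 per 1000 (43%) |
| 1.5 | 14.8 (49%) | 15.7 (52%) |
| 2 | 16.9 (56%) | 18.2 (61%) |

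Power for a 30% reduction (9 per 1000) at DEFF 1: 9 / 4.59 = 1.96, and 1.96 − 1.96 ≈ 0, so power is about 50%.

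*DID at other assumed event rates* (the document gives no rate for death on day 0 or before day 7), with 0.03 replaced by p in all four cells, DEFF 1:
- 10 per 1000: 7.5 per 1000 (75%)
- 15 per 1000: 9.1 (61%)
- 20 per 1000: 10.5 (52.5%)
- 40 per 1000: 14.7 (37%)

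*Matching, merged Ghana sample, n = 8876*, treated as a plain two-group comparison at 30 per 1000. With a 50:50 split at DEFF 1, a 31.1% reduction takes 30 to 20.7 per 1000. Then SE = √((0.0291 + 0.0202)/4438) = 0.00333 and 0.00933 / 0.00333 = 2.80, as required. For an assumed exposed share of 30–70%:
- DEFF 1: 31–34%
- DEFF 1.5: 37–41%
- DEFF 2: 43–47%

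Ghana 2008 against 2014 (2992 against 5884) gives 32% at DEFF 1 and 44% at DEFF 2. These figures ignore units lost in matching.

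*Primary outcomes, DID*, assumed prevalence 50–78%: 3.1–3.7 percentage points at DEFF 1, 4.4–5.3 at DEFF 2, and 6.2–7.5 at DEFF 4.

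**The case against.** **On the threshold.** The entry is one cell of a phase timetable, under preliminary analysis; the analysis text says 0.05 twice, and 0.5 is almost certainly a slip. That is fair as to intent. It does not remove the contradiction, because the table is said to govern implementation and several tests have no other stated level.

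A reader might go on to infer large consequences: a 97% chance of at least one false positive over five outcomes (1 − 0.5⁵ = 0.969), or 4.5 of the nine screened covariates passing by chance (9 × 0.5). The document does not support these as results of the plan. The first needs independent tests, but Table 5 nests the three mortality outcomes: day-0 deaths fall within deaths before day 7, and those within deaths before day 28. The second needs all nine covariates to be null, although the Conceptualization section presents several as known drivers. It also needs 0.5 to govern the screening, where the Data analysis section already sets 0.05 for the outcome–covariate tests.

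**On power.** The mortality outcomes are secondary, the data are existing surveys whose size cannot be changed, and for the primary outcomes the sample is ample. All of that stands, and it is why the remedy is to narrow the claim.

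A reader might also infer that mortality effects below 43% cannot be detected. That is too strong. An 80%-power difference is not a detection limit: a 30% reduction has about 50% power under the DID. The 43% belongs to one outcome, one method and no design effect, while the matching analysis does better. Nor does any section say that a non-significant mortality result would be read as no policy impact.

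**Conclusion.** Both points hold as separate matters.

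1. Table 6 is wrong as written. Its level is ten times the one used elsewhere, and for the primary-outcome tests, the DID and the matching it is the only level that could be read as applying. This conclusion needs no assumption.

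2. The general power claim is unsupported for mortality. For neonatal death the DID reaches 80% power only for reductions of about 43% before any design effect, and about 49–61% at design effects of 1.5 to 2. Matching on the merged Ghana sample reaches it at about 31–34%, rising to 43–47% at a design effect of 2. These figures rest on the document's n and its 30–31 per 1000, together with assumed two-sided 0.05, 80% power, the design effects and the exposed share. The size of the shortfall varies with outcome and method, so no single figure describes mortality as a whole. For antenatal care uptake and facility delivery the adequacy claim is reasonable.

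**What to change.** - In Table 6, Phase I, replace ≤ 0.5 with < 0.05. State once in Data analysis that this level applies to all tests, including the t-tests on the primary outcomes, the DID and the matched treatment effect.
- In Data source and size and in Data analysis, restrict the adequacy statement to antenatal care uptake and facility delivery, and drop the appeal to the surveys' own sample size calculation as the basis of power for mortality.
- Say that the mortality analyses have limited power, giving the figures above with their assumptions, and report those estimates with confidence intervals.

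The cost is one corrected digit, a few reworded sentences and a short statement of detectable differences. No data, design or analysis changes; the stated power for mortality becomes less favourable.
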